#### OLSA test

The OLSA test (HörTechGmbH, Germany) is a versatile examination that is structured into two randomized lists of 30 sentences of five-word, semantically unpredictable [40]. This tool is administered after a training session to minimize the learning curve. The test is carried out using a closed-set response format.

The test yields the Signal to Noise Ratio (SNR) measurement in dB at which the subject recognizes 50 % of the words presented.

The test is administered using the S0N0 presentation setup (speech and noise from the same frontal loudspeaker).The background noise is presented at 65 dB SPL whereas the speech level is adaptively adjusted depending on the subjects’ response to obtain the SNR.

Puglisi et al. (2015) described the reference ranges and standard deviations of the OLSA test for the Italian language by determining different levels to identify at-risk patients [19].The cutoff of the SNR dB (SRT) among the older adults was set to – 0.4 dB based on a reference mean level of -6.7 plus 2 standard deviations [19].

### Statistical considerations:

An intrasubject endpoint comparison is to be used for primary and secondary study objectives. The pairwise comparisons are of interest: previous use of HA (Pre)-to-12 months HA use (Post).

Investigation will apply multivariate exploratory factor analysis to reduce the number of variables and identify possible latent factors, followed by Spearman correlation to analyze the relationships between the variables and the factors.Finally regression analysis will apply to investigate how factors and variables relate to each other and how they predict outcomes.

Data will be analyzed by nonparametric tests for categorical variables and by t-test for continuous variables.

Questionnaires analysis will be performed by using a nonparametric test.

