## Methods and design

### Study aims

The primary aim of this study is to identify whether or not there is any significant improvement in speech recognition in noise in older adults patients ( > = 65 years) who are using HA for the first time. This improvement is to be verified by using a Signal to Noise Ratio (SNR) reduction which will be evaluated using the OLSA test.The secondary aim is to process the correlations between the use of the HA and quality of life and cognitive status in older adults. Any improvement or deterioration can be seen in higher or lower scores in auto-assessment questionnaires.

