### Study design

This is a prospective observational, repeated measurement, single-subject design study.

Changes in speech recognition by noise score, health-related quality of life, and overall well-being are assesses.

The study design is monocentric and is conducted at the outpatient service of the ENT Department of the “Saliceto” Hospital in Piacenza, Italy.

All the materials used are appropriate for the italian language.

This study is registered with the Ethics Committee of the Area Vasta Emilia Nord under number 104; date of approval 17/07/2017.

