### Subjects

Study subjects who use unilateral or bilateral hearing aids for the first time are to be included. Eligible participants are consecutively identified on the HA registry of the Local Unit of the National Health System (NHS). The Italian NHS is a welfare system which totally or partially funds the HA costs of the patients selected.

Subjects are > = 65 years old using unilateral or bilateral HA for the first time. According to local NHS threshold-criteria for funding adult HAs, the best ear of the patients must have a Pure-Tone Average (PTA) > = 45 dB HL. PTA is the average air-tonal threshold at 500, 1000, 2000, and 4000 Hz frequencies.

Only the subjects who signed the Patient Informed Consent Form prior to the first assessment (baseline, t0) are eligible for the clinical investigation.Approximately 100 individuals will be included. The sample size of 100 people was recruited according to a previous preliminary study by the authors (Tognola et al. 2019) and depending on olderpopulation eligible to utilize HA. Indeed, eligible participants are consecutively identified in the HA registry of the Local Unit of the National Health System (NHS).

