## Discussion

This study aims to show the potential positive effect of HAs on auditory skills and on quality of life of older adults with hearing loss. In particular, the efficacy of HA in speech perception in noisy environments and the improvement of quality of life in the older adults using HA for the first time is to be evaluated. The broad approach will lead to a greater understanding of how hearing impacts the quality of life in older adults thereby improving healthy aging.

Since the older adults are increasing in number in the Italian population, a greater number of hearing aids will be required to treat this growing presbycusic population. This will strongly affect the finances of the National Health System, which bears the full or partial cost of HA in most cases. This is also a good reason to understand the real benefits of the HA application clearly. The study outcomes are intended to provide transparent and comparable evidence-based information for healthcare policymakers by supporting the provision of health services for the treatment of hearing loss.

The comprehensive protocol considers a range of widely accepted, interrelated metrics associated with aging in addition to functional hearing. The use of this protocol does not propose the investigation of causal effects but rather investigation of the pre-post HA candidates by observing long-term health outcomes.

The primary endpoint of this study is to identify significant improvement in speech recognition in noise. The percentage of subjects with SNR > 1.5 dB at OLSA test is to be evaluate in order to verify the endpoint.

The OLSA test is the tool most frequently used to find the auditory outcome in noisy environment in the majority of the recent literature. Use of this test has overcome the traditional speech audiometry because it uses sentences consisting of a matrix of 5 semantically unpredictable words and is based on an adaptive method. This has overcome the memory capacity of HA users who perform speech audiometry several times at follow up and are able to learn the words in the lists. Furthermore, in contrast to speech audiometry with sentences of common use that have a semantic context, the OLSA test does not have a predictable semantic context.

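### The primary endpoint is verified by a percentage with no direction, change or reference rate, while the aims and statistics sections point to a within-subject reduction in SNR

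*Protocol article*

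**What the plan says.** Three places in the protocol article bear on the primary question.

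- Study aims: the improvement is a fall in SNR on a continuous dB scale. "This improvement is to be verified by using a Signal to Noise Ratio (SNR) reduction which will be evaluated using the OLSA test".
- Statistical considerations: "An intrasubject endpoint comparison is to be used for primary and secondary study objectives", with Pre and 12-month Post as the pair. The tests are given in general terms: "Data will be analyzed by nonparametric tests for categorical variables and by t-test for continuous variables".
- Discussion: "The primary endpoint of this study is to identify significant improvement in speech recognition in noise". The next sentence states how this is decided: "The percentage of subjects with SNR > 1.5 dB at OLSA test is to be evaluate in order to verify the endpoint".

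The design has one group: "This is a prospective observational, repeated measurement, single-subject design study". On size, the article says "Approximately 100 individuals will be included". It bases this on a preliminary study and on the number of eligible older people, and it shows no effect size, alpha or power.

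**The concern.** The Discussion names a proportion as the quantity that settles the primary endpoint. The other two sections lead to a mean change. A t-test on SNR does not test that proportion, and the article does not say which of the two decides.

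The proportion is also not usable as written. It is a level (SNR above 1.5 dB) with no mention of Pre, Post or change. Because the aim is a lower SNR, a value above 1.5 dB is a poor result if taken literally. If an improvement of more than 1.5 dB is meant, no rate is given against which to judge the observed percentage, and there is no control group to supply one.

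What is at stake is the primary conclusion. Two analysts following different sections could reach opposite answers from the same data, in a study whose stated purpose includes informing health policy.

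**Working it through.** The plan has no power, alpha, effect size or null rate to reproduce, so the check asks whether the two quantities can disagree and by how much.

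**Inputs**
- Threshold 1.5 dB (Discussion), read here as a Pre-to-Post improvement.
- n = 100 (Subjects).
- SD of the Pre-Post change: not given, so a range is assumed. The only OLSA SD that can be derived comes from the OLSA test section, where the cutoff of -0.4 dB is the reference mean of -6.7 dB plus 2 SD: (-0.4 + 6.7)/2 = 3.15 dB. This is a between-subject reference SD, not the SD of a change.
- Changes are assumed to be normally distributed.

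**Step 1. Share improving by more than 1.5 dB when the true mean change is 0**

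P = 1 − Φ(1.5/SD)

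| SD of change (dB) | 1.5/SD | Chance share |
|---|---|---|
| 0.5 | 3.00 | 0.1% |
| 0.7 | 2.14 | 1.6% |
| 1.0 | 1.50 | 6.7% |
| 1.5 | 1.00 | 15.9% |
| 2.0 | 0.75 | 22.7% |
| 3.0 | 0.50 | 30.9% |
| 3.15 | 0.48 | 31.7% |

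If 3.15 dB held at both visits with Pre-Post correlation r (assumed), the SD of change would be 3.15 × √(2(1 − r)). For r = 0.5, 0.8, 0.9 and 0.95 this gives 3.15, 1.99, 1.41 and 1.00 dB, and chance shares of 31.7%, 22.6%, 14.4% and 6.6%.

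**Step 2. What an observed percentage would have to exceed**

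For illustration, take an exact one-sample binomial test at one-sided 0.025 with n = 100. At least 13 responders are needed if the chance rate is 6.7%, 23 if 14.4%, 32 if 22.7% and 42 if 31.7%. An observed 20% would therefore be convincing in the first case and unremarkable in the other three.

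**Step 3. Disagreement in both directions at n = 100**
- Real mean gain of 0.5 dB, SD of change 1 dB. The standard error is 1/√100 = 0.1 dB, so the power of the paired comparison is about Φ(0.5/0.1 − 1.96) = Φ(3.04), or 99.9%. The share exceeding 1.5 dB is 1 − Φ((1.5 − 0.5)/1) = 15.9%.
- No true change, SD of change 3.15 dB. About 32% exceed 1.5 dB, while a two-sided 5% paired t-test is non-significant 95% of the time.

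The low percentage therefore goes with the real gain and the high one with no gain.

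**Step 4. The literal reading**

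If 1.5 dB is an absolute SNR, the percentage could be taken at Pre and at Post, and Pre would be the reference. Steps 1 and 2 would then not apply. However, the article states no such comparison, and a higher percentage would mean worse recognition in noise.

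**The case against.** The strongest reply has four parts.

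1. The threshold is worded as a level. On that reading Pre supplies the reference, and the statistics section plans Pre-Post comparisons and also nonparametric tests for categorical data, which might cover a percentage. So the t-test is not the only planned test. This part stands: the chance-crossing figures hold only if an improvement is meant. But the nonparametric test is unnamed and is not linked to this percentage, and the level reading has the wrong direction for the aim.

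2. A reader might infer that a substantial responder rate would appear even without any effect. The article does not support that as a fact. It gives no SD of change, and at 0.7 dB or less the chance share is under 2%.

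3. A reader might also infer that any percentage above zero would count as success, or that the continuous information is thrown away. Neither is in the text. The article asks for significant improvement and plans tests, but gives no success rule for the percentage. It also retains a continuous comparison, so information is lost only if the percentage alone decides.

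4. Exact tests and thresholds belong in an analysis plan, and a journal article condenses. This is fair as far as missing detail goes. It does not remove the conflict, because the article itself names a deciding quantity that does not match its own aims and statistics sections.

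The sentence "An intrasubject endpoint comparison is to be used for primary and secondary study objectives" is not wrong in itself. The defect lies in the Discussion's verification rule and its mismatch with the other two sections.

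**Conclusion.** The point holds in a limited form. The article does not fix one primary quantity, and the one it calls decisive has no direction, no stated change and no reference rate.

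The consequence is conditional. If 1.5 dB means improvement and changes are normal, the share expected with no true change runs from near 0% (SD of change 0.5 dB) to about 32% (3.15 dB). The article does not allow a choice within that range. The lack of a reference rate on the improvement reading, and the mismatch with the t-test, do not depend on the SD.

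That the two quantities can lead to opposite conclusions is shown by the two scenarios at n = 100, both of which use assumed SDs.

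**What to change.** - Name one primary analysis: the mean within-subject change in OLSA SNR, Post minus Pre, with a paired t-test and 95% CI. Improvement is shown if the upper limit is below 0. This agrees with the Study aims and Statistical considerations.
- Reword 1.5 dB in the Discussion as a Pre-to-Post reduction, with its direction stated.
- Report the percentages improving and worsening by at least 1.5 dB side by side, as supportive description only. The worsening share gives a rough internal gauge of how often the threshold is crossed by chance.

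The cost is wording: no new data or visits are needed. The downside is that the headline becomes a mean in dB and not a percentage. The change does not turn the result into a device effect. It remains an uncontrolled pre-post change, which fits the article's own statement in the Discussion that it does not set out to study causal effects.

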## Discussion

This study aims to show the potential positive effect of HAs on auditory skills and on quality of life of older adults with hearing loss. In particular, the efficacy of HA in speech perception in noisy environments and the improvement of quality of life in the older adults using HA for the first time is to be evaluated. The broad approach will lead to a greater understanding of how hearing impacts the quality of life in older adults thereby improving healthy aging.

Since the older adults are increasing in number in the Italian population, a greater number of hearing aids will be required to treat this growing presbycusic population. This will strongly affect the finances of the National Health System, which bears the full or partial cost of HA in most cases. This is also a good reason to understand the real benefits of the HA application clearly. The study outcomes are intended to provide transparent and comparable evidence-based information for healthcare policymakers by supporting the provision of health services for the treatment of hearing loss.

The comprehensive protocol considers a range of widely accepted, interrelated metrics associated with aging in addition to functional hearing. The use of this protocol does not propose the investigation of causal effects but rather investigation of the pre-post HA candidates by observing long-term health outcomes.

The primary endpoint of this study is to identify significant improvement in speech recognition in noise. The percentage of subjects with SNR > 1.5 dB at OLSA test is to be evaluate in order to verify the endpoint.

The OLSA test is the tool most frequently used to find the auditory outcome in noisy environment in the majority of the recent literature. Use of this test has overcome the traditional speech audiometry because it uses sentences consisting of a matrix of 5 semantically unpredictable words and is based on an adaptive method. This has overcome the memory capacity of HA users who perform speech audiometry several times at follow up and are able to learn the words in the lists. Furthermore, in contrast to speech audiometry with sentences of common use that have a semantic context, the OLSA test does not have a predictable semantic context.

During this study two-time point, tonal unaided audiometry was used to check any auditory threshold modification and worsening of the audiometric clinical situation over time. Speech audiometry in unaided conditions in the first assessment and in aided conditions in the second assessment were used because it describes the sample and allows it to be compared to the existing literature.

The second objective of this study is based on the evaluation of possible improvements in the overall health-related quality of life in the sample.

To verify this aim, self-report questionnaires were chosen, which are essentially non-verbal and consequently remove challenges directly associated with utilizing new HA. The percentage of subjects who improve the questionnaire score using HA (second assessment) compared to the first evaluation in unaided conditions is to be evaluated.

Improvement in quality of life can be evaluated by using different questionnaires. The AQoL questionnaire is used in this study because of its robust psychometric characteristics and wide diffusion in the health-related quality of life literature. In a review by Mihalopoulos et al., (thatanalyzesinstruments for depression outcome measurements) report that AQoL-8D “had the highest correlation with the disease-specific measurements and the best goodness-of-fit transformation properties” [28].

The HHIE has been included in the study in order to better understand the effects of hearing impairment on emotional and social adjustment in everyday life. It is one of the most widely applied questionnaires with respect to auditory participation and has been reported with both HA and cochlear implant recipients [41]. A significant reduction of the questionnaire score in Post vs. Pre-evaluation is expected in this study, which suggests quality of life improvement.

The MoCA questionnaire was chosen to screen the cognitive abilities of subjects. The use of this questionnaire will exclude deficits in these abilities. Using this test in Pre and Post evaluation will verify that cognitive abilities do not affect other questionnaires and HA results. The use of the MoCA questionnaire in the Pre and Post evaluation will exclude a reduction of the cognitive abilities over time. A reduction of these abilities can be a sign of the deterioration of the general state of health that may affect the execution of the other questionnaires used. The same score is expected in Pre and Post evaluation of the same subject.

The APHAB questionnaire is used to assess problems in speech understanding in different listening situations. This self-assessment is one of the most used questionnaires in clinical practice. An improvement in the scores in Post evaluation compared to Pre evaluation will verify a reduction of listening problems secondary to HA usage.

The IOI-HA questionnaire is only used in the Post evaluation. It will help understand the difficulties and benefits of HA use perceived by the patients. In particular, this questionnaire will give us a picture of the HA outcomes in different areas. Furthermore, being a standardized questionnaire, it will facilitate comparison of the sample with the existing literature.

The strength of this study lies in evaluating the auditory and health outcomes over time which contrasts with most of the recent studies that show an overview of the outcomes at a precise moment and various other biased sources.

Furthermore, as reported by Hanratty and Lawlor, people over 70 are thought to have a hearing impairment that would benefit from a HA but a high percentage of these people probably never use their aid [12]. The study presented in this paper can not only underline the benefits but also real HA usage over time. This information is very important for healthcare policy because the Italian National Health System bears all or some of the HA costs for most of these patients.

These outcomes should contribute to providing key actors of the health system with means of enhancing their part in a collective endeavor targeting the best care and quality of life for older adults citizens because general well-being translates into healthy aging.

The single-subject, repeated-measures design allows for subjects to serve as their own controls, and thus increases statistical power. The relatively large population size helps provide a good estimate of effect size and would make the results broadly applicable.

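### The primary endpoint rule is printed as an absolute OLSA level above 1.5 dB, with no visit, change or sign, and taken literally it conflicts with the plan's own definition of improvement as an SNR reduction

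*Protocol article*

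**What the plan says.** The Discussion names the endpoint, "The primary endpoint of this study is to identify significant improvement in speech recognition in noise", and the next sentence says how it will be checked: "The percentage of subjects with SNR > 1.5 dB at OLSA test is to be evaluate in order to verify the endpoint".

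Three other places bear on how that sentence can be read:

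- **Direction of benefit (Study aims):** "This improvement is to be verified by using a Signal to Noise Ratio (SNR) reduction which will be evaluated using the OLSA test".
- **What the number is (OLSA test):** "The test yields the Signal to Noise Ratio (SNR) measurement in dB at which the subject recognizes 50 % of the words presented". The same section says that the cutoff "among the older adults was set to – 0.4 dB", "based on a reference mean level of -6.7 plus 2 standard deviations".
- **Type of comparison (Statistical considerations):** "An intrasubject endpoint comparison is to be used for primary and secondary study objectives". The comparison is Pre against 12 months of use, and t-tests are planned for continuous variables.

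The article gives no derivation of 1.5 dB and no percentage at which the endpoint would count as verified.

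**The concern.** The OLSA result is the SNR a listener needs in order to understand half the words, so a lower value is better. A rule that counts values above 1.5 dB therefore selects the unfavourable side of the scale, although it is offered as the check on an improvement. It also sets a level for a single measurement, whereas the Statistical considerations promise a comparison within each subject.

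This is the only numerical criterion attached to the primary aim. If its meaning is left open, the analyst can choose among several readings after seeing the data, and some of them move in opposite directions for the same benefit. The Discussion says that the results are intended for healthcare policymakers, so the headline percentage should have one meaning.

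**Working it through.** **1. Inputs from the article.** Rule: SNR above 1.5 dB (Discussion). Cutoff -0.4 dB and reference mean -6.7 dB, with the cutoff equal to mean plus 2 SD (OLSA test). Benefit is a reduction (Study aims).

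**2. The article's own OLSA figure.** The SD is not stated, so the cutoff cannot be reproduced independently. Solving for the SD gives (-0.4 + 6.7)/2 = 3.15 dB, and -6.7 + 2 × 3.15 = -0.4 dB.

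**3. Where +1.5 dB lies on that scale.**

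- Against the cutoff: 1.5 - (-0.4) = 1.9 dB worse.
- Against the reference mean: 1.5 - (-6.7) = 8.2 dB worse, or 8.2/3.15 = 2.60 SD. Under normality about 0.5% of the reference group would exceed it.

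**4. Literal reading: share of subjects above +1.5 dB.** If every subject's SNR falls or stays the same, this share cannot rise, whatever the distribution. To show the size, assume normal SNR with the same SD at both visits and compute share = 1 - Φ((1.5 - mean)/SD). The means and SDs for the cohort are assumptions; the article gives none.

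| Assumed SD | Pre mean | Post mean | Share at Pre | Share at Post |
|---|---|---|---|---|
| 2 | +3 | 0 | 77% | 23% |
| 3 | +3 | 0 | 69% | 31% |
| 4 | +3 | 0 | 65% | 35% |
| 3.15 | -2 | -5 | 13.3% | 2.0% |
| 3.15 | 0 | -3 | 31.7% | 7.7% |
| 3.15 | +2 | -1 | 56.3% | 21.4% |
| 3.15 | +4 | +1 | 78.6% | 43.7% |

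Every row has the same 3 dB benefit. The direction is always downward; the size depends heavily on the assumed starting point.

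**5. Change readings.** Assume SD 3.15 dB at each visit and a Pre-Post correlation of 0.7 (also an assumption). The SD of the change is 3.15 × √(2 × (1 - 0.7)) = 2.44 dB.

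- *Pre minus Post above 1.5 dB:* share = 1 - Φ((1.5 - d)/2.44), where d is the true mean reduction. It gives 27%, 42%, 50% and 73% for d = 0, 1, 1.5 and 3 dB, so it rises with benefit.
- *Post minus Pre above 1.5 dB:* share = 1 - Φ((1.5 + d)/2.44). It gives 27% for d = 0, and for d = 3 dB, 1 - Φ(4.5/2.44) = 1 - Φ(1.84), about 3%. It counts subjects who got worse.

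**6. Readings side by side.** The printed words allow (a) a level, with a higher share counted as favourable; (b) a level, with the share compared between Pre and Post and a fall counted as favourable; (c) a reduction of more than 1.5 dB; (d) an increase of more than 1.5 dB. Only (b) and (c) agree with the Study aims, and only (c) is a within-subject criterion in the full sense of the Statistical considerations. The sentence does not say which applies.

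**The case against.** The strongest reply is that the inversion comes from isolating one sentence. The sentence before it speaks of improvement, the Study aims define improvement as a reduction, and the Statistical considerations specify a within-subject comparison. For the questionnaires, the Discussion sets a parallel rule based on subjects who improve on their first evaluation. Together these point to a reduction of more than 1.5 dB. This stands: the intended meaning can probably be recovered, and the defect is most likely one of wording.

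A reader might go further and infer that the plan scores its worst performers as successes and will report the wrong direction. The article does not support that. It never uses the word success for this percentage and sets no pass mark. Comparing the share above 1.5 dB at Pre with the share at Post keeps the printed words and runs the right way: a fall from 69% to 31% would then show benefit. The planned t-test for continuous variables would also give the primary aim a directional comparison that does not depend on this sentence.

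It can also be said that visits and sign conventions belong in a fuller document that is not shown. That would answer a complaint about missing detail. It does not answer this one, because the article does state a rule, and the rule as printed disagrees with three of its own sections. The article can be explicit about direction: for the APHAB it says which score is subtracted from which.

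**Conclusion.** The point holds as a mis-stated decision rule for the primary endpoint. As printed, it is a level on the poor-performance side of the scale, 1.9 dB beyond the article's own cutoff. It does not fit an aim defined as an SNR reduction or a comparison defined within subjects. Taken as the share that verifies improvement, it falls as benefit grows; taken as Post minus Pre, it counts deterioration.

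The 1.9 dB and 8.2 dB distances come directly from the article. The literal share's downward direction needs no assumed mean or SD if SNR shifts downward. All the percentages are illustrations under assumed normality, means, SDs and correlation, and do not predict this cohort's results.

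What is established is that readings with opposite directions remain open, not that the trial will reach a wrong conclusion. Nor do the documents confirm that 1.5 dB is a suitable change threshold.

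**What to change.** Replace the sentence in the Discussion with a signed rule, keeping the printed strict inequality: *the percentage of subjects whose OLSA SNR falls by more than 1.5 dB from Pre to Post (Pre minus Post > 1.5 dB)*. Before adopting it, the sponsor should confirm that 1.5 dB was meant as a change threshold and give its source.

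If a level was meant, say instead that the percentage of subjects above 1.5 dB is compared between Pre and Post and that a decrease indicates benefit.

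Under either version, state what result would count as verifying the endpoint. The cost is one or two sentences and a source for the threshold. No new data, visits or tests are needed, and the choice should be recorded before the Post data are analysed.
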